### Sample size

The study is powered for the primary endpoint, that is, decrease of mean SOFA score by at least 1.4 points on day 9. In order to calculate the power of the study, the following hypotheses are made: according to data from the previous RCTs in sepsis VISEP^9^ and MAXSEP^10^ on a total of 1137 patients, there is a significant association between the mean total SOFA score at day 9 and 28-day mortality. A reduction of the primary endpoint by 1.4 points is expected to be associated with a reduction of 28-day mortality. Based on the preliminary results of the PROVIDE Study (ClinicalTrials.gov NCT0333225), 40% of the enrolled patients in each arm will be recruited with fulminant hyperinflammation and another 60% for sepsis-associated immunoparalysis. The study is powered for 90% at the 5% level of significance and the anticipated mean difference in the SD between the two groups will be 3.2. In order to detect this difference of 1.4 points in the mean SOFA score, 117 patients will be needed per trial arm. Considering a drop-out rate of about 15%, a total of 280 patients need to be randomised.

### Statistical analysis

The endpoints of the change of the mean SOFA score will be compared between the two groups of treatment using the Welch’s t-test for mean differences. The endpoints of time to an event will be analysed using Cox regression analysis. Analysis will be done in the intention-to-treat population with sensitivity analysis for the per-protocol population. Missing values will be imputed by last observation carried forward.

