## Methods and analysis

### Study design and setting

ImmunoSep is a prospective randomised placebo-controlled phase 2 clinical trial in a total number of 24 academic and non-academic study sites in Greece, Germany, Switzerland, the Netherlands and Romania aiming to assess whether personalised adjunctive immunotherapy directed against a state of either fulminant hyperinflammation or immunoparalysis is able to improve sepsis outcomes. Patients will be selected by a panel of biomarkers and laboratory findings and will be allocated to placebo or immunotherapy treatment according to their needs by 1:1 ratio. The study enrolment will be competitive between the participating study sites targeting 280 participants.

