### Study intervention/allocation to blind treatment

The unblinded pharmacists receive information on the daily preparation of the study drug by the site https://sepsisonline.org where they have to log-in using a secure username and password. Once a patient is considered eligible for enrolment, he will be allocated blindly 1:1 to one of the two groups of treatment. The randomisation is stratified by study site and it is done using one computer-generated sequencing. The preparation of the study drug will be done in each study site by the unblinded pharmacist investigators. The two groups of treatment are:

**Placebo**. In addition to standard-of-care treatment decided by the attending physicians, patients will also receive intravenously 20 mL (10 mL for patients when creatinine clearance is lower than 30 mL/min) 0.9% saline (N/S) three times a day (every 8 hours) for 15 days and 0.5 mL subcutaneously 1 mL 0.9% N/S every other day for a total of 15 days.**Active immunotherapy**. In addition to standard-of-care treatment decided by the attending physicians, patients with MALS will receive 200 mg anakinra every 8 hours and subcutaneous placebo as specified above, whereas patients with immunoparalysis will receive intravenous placebo as specified above and subcutaneous 100 µg rhIFNγ once every other day for a total of 15 days. Creatinine clearance should be calculated daily by the Cockcroft Gault equation and when it is lower than 30 mL/min, anakinra will be given at half dose.

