### Study procedures

An overview of all study procedures is provided in table 1. Briefly, visits 1–15, visit 21, visit 28 and visit 90 include recording of co-administered drugs; SOFA score; vital signs; absolute blood cell count and differentiation, haemoglobin and absolute platelet count (if available); biochemistry (if available); coagulation (if available); blood gasses (if available), microbiology and antibiogram (if available). There would also be recording of the clinical state of the infection making the patient eligible for the study. Of utmost importance is recording and subsequently properly reporting any adverse event/serious adverse event occurring during trial participation. At visit days 1, 2, 4, 7, 15, 21, 28 and 90, blood sampling for trial-related purposes is drawn (transcriptomic, flow cytometry, cytokine production, ATAC-epigenome sequencing, proteomic analysis) and microbiome samples from nares, oral cavity and rectum. All collected samples are pseudoanonymised using a 9-digit code. Separate coding is done per study site.

**Table 1 T1:** Study visits

Day	Study visits																		
	0	1	2	3	4	5	6	7	8	9	10	11	12	13	14	15	21	28	90
Obtain ICF	X																		
Study drug		X	X	X	X	X	X	X	X	X	X	X	X	X	X	X			
SOFA score		X	X	X	X	X	X	X	X	X	X	X	X	X	X	X	X		
Medical history		X																	
Clinical state of infection							X	X	X	X	X	X	X	X	X	X	X		
Survival		X	X	X	X	X	X	X	X	X	X	X	X	X	X	X	X	X	X
Vital signs		X	X	X	X	X	X	X	X	X	X	X	X	X	X	X	X		
Lab tests		X	X	X	X	X	X	X	X	X	X	X	X	X	X	X	X		
Microbiology		X	X	X	X	X	X	X	X	X	X	X	X	X	X	X	X		
Blood collection		X	X		X			X								X	X	X	X
Microbiome samples		X	X		X			X								X	X	X	X
Co-administered medication		X	X	X	X	X	X	X	X	X	X	X	X	X	X	X	X		
Adverse events			X	X	X	X	X	X	X	X	X	X	X	X	X	X	X	X	X

ICF, informed consent form; SOFA, Sequential Organ Failure Assessment.

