### Study endpoints

The primary efficacy endpoint is the difference in the mean total SOFA score until day 9 after randomisation between the two groups of treatment. The time frame of 9 days for the assessment of the primary endpoint is based on previous experience coming from the VISEP^9^ and MAXSEP^10^ RCTs where this endpoint was used to assess an impact of treatment on sepsis-induced organ dysfunction at day 9.

The secondary study endpoint is the comparison of the two groups of treatment on: (a) 28-day all-cause mortality; (b) 90-day all-cause mortality; (c) the mean total SOFA score on day 15 from randomisation; (d) the impact of personalised immunotherapy on the reversal of MALS or immunoparalysis on day 15 from randomisation, defined for patients with MALS as at least 15% decrease of the baseline serum ferritin, and for patients with immunoparalysis as restoration of HLA-DR expression on CD45/CD14 monocytes above 8000/cell. The assessment of the mean total SOFA score on day 15 from randomisation is a read-out of treatment efficacy at the end of treatment. It is considered that a later time point of assessment of the mean total SOFA score is not needed since mortality is the secondary endpoint already assessed at a later time point.

Exploratory study endpoints are: (a) the impact of personalised immunotherapy on the resolution of infection leading to study enrolment on day 15 after randomisation; and (b) the development of genomic, epigenomic, proteomic, metabolomic and microbiomic surrogate biomarkers for the primary and secondary endpoints. This will come from the exploitation of the genomic and proteomic material that will be analysed by the partners of the ImmunoSep Project.

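### The primary SOFA comparison is an unadjusted Welch t-test, which gives up precision that baseline SOFA and, to a small degree, site could provide

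*Protocol article*

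**What the plan says.** The protocol article, Statistical analysis, says "The endpoints of the change of the mean SOFA score will be compared between the two groups of treatment" and names Welch's "t-test for mean differences". It mentions no covariate and no stratum term for this comparison.

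Three other places bear on the choice:

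- **Outcome.** Study endpoints defines the primary endpoint as the "difference in the mean total SOFA score until day 9 after randomisation between the two groups of treatment". This is a level with nothing subtracted, whereas Statistical analysis speaks of a change and gives no reference point for it.
- **Allocation.** Study intervention/allocation to blind treatment says "The randomisation is stratified by study site". Study design and setting gives "a total number of 24 academic and non-academic study sites".
- **Data.** The second Study procedures section says that visits "include recording of co-administered drugs; SOFA score; vital signs". Table 1 shows SOFA daily on days 1 to 15. Study drug also starts on day 1, and no SOFA is listed on day 0.

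Sample size plans to "detect this difference of 1.4 points in the mean SOFA score" with an SD of 3.2, 90% power, a 5% level and 117 patients per arm.

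**The concern.** A patient's SOFA score at entry can be expected to say something about the SOFA score over the following days. A two-sample test on the outcome alone leaves that explained variation in the error term and leaves any chance imbalance in entry SOFA in the estimate. With 117 per arm and an assumed baseline SD of 3.2, the standard error of such an imbalance is 3.2 × √(2/117) = 0.42 points, against a target difference of 1.4.

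Subtracting baseline is only a partial remedy. It forces the regression slope on baseline to be 1, where ANCOVA would estimate it. Under either reading of the endpoint, therefore, the named test is in large samples no more precise than ANCOVA and usually less.

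Stratifying allocation by site removes some between-site variation from the treatment contrast. A test with no site term still counts that variation in its standard error, which is then slightly too large.

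At stake are the width of the confidence interval and the smallest effect that this phase 2 trial can detect.

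**Working it through.** **Inputs from the protocol article.** Difference 1.4, SD 3.2, power 90%, level 5%, 117 per arm, about 15% drop-out, 280 in total (Sample size); 24 sites (Study design and setting). The test is taken as two-sided, and 3.2 as a common SD, because the article's wording of the SD is unclear.

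**Assumptions not in the article.** The correlation r between baseline SOFA and the outcome, 0.4 to 0.7; equal variance at baseline and outcome; the site intraclass correlation (ICC), 0.01 to 0.10.

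**Step 1: the plan's own figure.** n per arm = 2 × [3.2 × (1.960 + 1.282) / 1.4]² = 109.8, so 110, or 111 by the exact t distribution. The stated 117 is somewhat larger, which is on the safe side. At 117 per arm the standard error is 3.2 × √(2/117) = 0.418, the noncentrality is 1.4/0.418 = 3.35, and power is 91.5%. The stated 90% is met without adjustment. For drop-out, 117/0.85 = 137.6, so 138 per arm or 276 in total, close to 280.

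**Step 2: ANCOVA when 3.2 is the SD of the raw score.** Residual SD = 3.2 × √(1 − r²), and variance falls by r².

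| r | Variance reduction | Residual SD | Power at 117 per arm |
|---|---|---|---|
| 0 (unadjusted) | 0% | 3.20 | 91.5% |
| 0.4 | 16% | 2.93 | 95.3% |
| 0.5 | 25% | 2.77 | 97.1% |
| 0.6 | 36% | 2.56 | 98.6% |
| 0.7 | 49% | 2.29 | 99.7% |

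The difference detectable with 90% power (normal approximation) goes from 1.36 unadjusted to 1.24 at r = 0.4 and 0.97 at r = 0.7.

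**Step 3: if change from baseline is tested.** With 3.2 as the raw-score SD, the change-score SD is 3.2 × √[2(1 − r)].

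| r | Change-score SD | Power at 117 per arm |
|---|---|---|
| 0.3 | 3.79 | 80.4% |
| 0.4 | 3.51 | 86.0% |
| 0.5 | 3.20 | 91.5% |
| 0.7 | 2.48 | 99.0% |

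The change score is worse than the raw score below r = 0.5, equal to it at 0.5 and better above. At every r shown, ANCOVA does at least as well as either.

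If 3.2 is already the change-score SD, the plan's 91.5% applies to the change score. The ANCOVA residual SD is then 3.2 × √[(1 + r)/2], a variance reduction of (1 − r)/2: 30% at r = 0.4 (power 97.9%) and 15% at r = 0.7 (power 95.1%).

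**Step 4: site.** Adjusting for site alone gives SD = 3.2 × √(1 − ICC), a variance reduction of 1% to 10%. Power at 117 per arm goes from 91.5% to 91.7% (ICC 0.01) or 94.0% (ICC 0.10). If arms are balanced within sites, the true two-sided level of the unadjusted test is about 2 × [1 − Φ(1.96/√(1 − ICC))], which is 0.049 at ICC 0.01 and 0.039 at ICC 0.10. Omitting site makes the test slightly conservative. There are on average 280/24 = 11.7 patients per site.

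**The case against.** The strongest defence is that nothing in the plan is broken. Under randomisation Welch's test is unbiased and valid, and on the article's own inputs it exceeds its power target. The size of any gain depends on a correlation that the article does not give. The article is also a condensed account, and an analysis plan that is not shown may add adjusted analyses. The first three statements are right and fix the weight of this point. The last is only a partial answer, because the article names the test for this endpoint, and a Welch test cannot carry a covariate.

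Four stronger readings are tempting and are not supported:

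- *The analysis is invalid because it does not follow the stratified randomisation.* Step 4 shows a small loss in the conservative direction.
- *The trial is underpowered, at 80% to 86%.* Those figures need three things together: a change-from-baseline outcome, 3.2 as the raw-score SD, and r of 0.3 to 0.4. At r = 0.7 the same test has 99.0% power, and if 3.2 is the change-score SD the shortfall disappears.
- *The plan certainly ignores baseline.* That follows from the Study endpoints wording. The Statistical analysis wording may mean that baseline is subtracted.
- *Adjustment is free because a baseline is already collected.* Table 1 starts SOFA and study drug on the same day, and the article does not say that the day-1 score precedes the first dose.

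**Conclusion.** The point holds as a matter of efficiency. The named primary test leaves out baseline SOFA or, if change from baseline is meant, uses it with a slope fixed at 1, and it leaves out the stratification factor. Neither validity nor the planned 90% power is in doubt.

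Most of the recoverable precision lies in baseline SOFA, with the size given in Steps 2 and 3; site is a minor addition. That ANCOVA is at least as precise in large samples does not depend on the assumed values, but the size of the gain does. The change is worth making because it costs little and helps under either definition of the outcome.

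**What to change.** 1. State one definition of the SOFA endpoint and use it in Study endpoints, Sample size and Statistical analysis, saying whether it is the mean up to day 9 or a change and, if a change, from which value. Say which quantity the SD of 3.2 describes.
2. Make the primary analysis an ANCOVA of that endpoint on treatment, baseline SOFA and site, with heteroscedasticity-robust standard errors so that the protection against unequal variances that Welch's test offers is kept. With about 12 patients per site, fit site as a random effect or pool small sites by country.
3. Define baseline SOFA as a value obtained before the first dose, and confirm that the day-1 record meets this.
4. Optionally add immune endotype. It determines which active drug a patient receives, Sample size expects a 40%/60% split, and it is not named as a stratification factor.
5. Keep Welch's t-test as a sensitivity analysis.

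The cost is a change of wording in the analysis section, fixed before unblinding. The sample size need not change. No new data are needed if the day-1 SOFA is a pre-dose value; if that is not assured, its timing has to be settled first.

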## Introduction

Sepsis is a life-threatening organ dysfunction that results from the dysregulated host response to an infection.^1^ Patients with sepsis-induced dysregulation present a broad spectrum of perturbation ranging from immune hyperactivation to immune suppression. In this respect, approximately 5%–10% of patients present mainly with fulminant hyperinflammation, an entity also known as macrophage activation-like syndrome (MALS),^2^ whereas a sizeable minority of other patients have mainly ineffective responses to secondary infections, a condition described as immunoparalysis.^3^

There is accumulating evidence that delivery of targeted immunotherapy for patients who present with these two extremes may improve outcome. Indeed, the post-hoc analysis of a randomised clinical trial (RCT) conducted more than 25 years ago showed that treatment with anakinra, the recombinant antagonist of the interleukin (IL)-1 receptor, provided 30% decrease of 28-day mortality among patients with hepatobiliary dysfunction and disseminated intravascular coagulation who bear phenotypical characteristics compatible with MALS.^4^ During the last years, we have suggested that serum ferritin can be an important diagnostic tool for MALS. Studying 5121 patients who were split into one test and into one validation cohort and studying another confirmation cohort from Sweden, it has been found that serum concentrations of ferritin greater than 4420 ng/mL had specificity 97.1% and 98% negative predictive value for the classification of MALS.^2^

On the other hand, the decrease of the expression of the human leucocyte antigen (HLA)-DR expression on the membrane of circulating monocytes is considered one of the hallmarks of immunoparalysis resulting in a dysfunctional immune response, which in turns leads to susceptibility for secondary infections, prolonged hospitalisation and increased mortality.^5^ The presence of immunoparalysis in patients with sepsis is associated with at least 50% risk of death in the subsequent 28 days.^6^ Evidence from human volunteers subjected to an endotoxin challenge suggests that immunoparalysis can be reversed by recombinant human interferon-gamma (rhIFNγ).^7^ In addition, when rhIFNγ was administered in nine patients with septic shock, reversal of immunoparalysis was also achieved.^8^

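### Last observation carried forward is the only stated missing-data rule for mean SOFA; read literally it freezes the score at death, so deaths barely count and harm can be understated or, if deaths come early, reversed

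*Protocol article*

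**What the plan says.** Statistical analysis: SOFA endpoints are "compared between the two groups of treatment using the Welch’s t-test for mean differences". On populations: "Analysis will be done in the intention-to-treat population with sensitivity analysis for the per-protocol population". On absent data there is one unqualified sentence: "Missing values will be imputed by last observation carried forward". The article gives no separate rule for death, discharge or any other kind of gap.

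Study endpoints: the primary endpoint is "the difference in the mean total SOFA score until day 9 after randomisation between the two groups of treatment". The Sample size section words it as "decrease of mean SOFA score by at least 1.4 points on day 9". Mean SOFA on day 15 is a secondary endpoint, and so is all-cause mortality at days 28 and 90.

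Expected deaths: the Introduction says immunoparalysis is "associated with at least 50% risk of death in the subsequent 28 days". The Sample size section expects 60% of patients in that group and 40% with hyperinflammation. The screening description gives MALS precedence because its mortality is higher. No death rate to day 9 is given. The strengths and limitations box states that the trial is not powered for mortality.

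**The concern.** A patient who dies on day 4 has no SOFA on days 5 to 9. If those days count as missing values, the stated rule fills them with the day-3 or day-4 score, so the patient enters the Welch test as if alive and unchanged. The same happens at any other gap, with the last recorded score standing in for the unknown course.

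The Sample size section justifies the endpoint by its association with 28-day mortality. Carrying forward weakens that link from the start: preventing a death moves the endpoint little, and causing one costs little. What is at stake is the direction and size of the primary result in a trial where deaths inside the window are to be expected. The day-15 SOFA endpoint has the same problem over a longer window.

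**Working it through.** **1. The plan's own scale.** Inputs from Sample size: difference 1.4, SD 3.2 (read as a common SD), 90% power, 5% level (taken as two-sided). n = 2 × (1.960 + 1.282)² × 3.2² / 1.4² = 110 per arm, or 111 with the t distribution. The article states 117, where power is 0.917. The excess is conservative and not part of this point. The yardstick below is 1.4.

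**2. How many deaths by day 9?** The article gives only the 28-day figure. *Assumption:* a 50% risk by day 28 with constant hazard. The risk by day 9 is then 1 − 0.5^(9/28) = 1 − 0.80 = 20%, or 28 of 140 per arm. The simulation in step 4 spans 12.5% to 29% on placebo (5/6 of the 15% to 35% on a fatal course die by day 9).

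**3. Algebra.** If an extra share q of one arm dies, carrying forward shifts that arm's mean by

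shift = q × (carried SOFA − SOFA had they lived).

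With q = 10%:

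- carried value 3 or 6 points lower: −0.3 or −0.6, a false benefit (21% or 43% of 1.4)
- carried value equal: 0, so the deaths are invisible
- carried value 3 or 6 points higher: +0.3 or +0.6, so harm shows

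The sign depends on whether SOFA had risen before death.

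**4. Simulation.** *Assumptions, none from the article:* baseline SOFA 9 (SD 3); survivors change by −0.35 per day; patients on a fatal course change by +0.8 per day and on placebo die on days 5-10; 15% to 35% are on a fatal course. There are 140 per arm and 600 runs per scenario, with Welch's test. Differences are active minus placebo; negative means apparent benefit.

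| Scenario in the active arm | Extra day-9 deaths (points) | Carried forward, day 1-9 mean | Carried forward, day 9 | Days after death = 24, day 1-9 mean |
|---|---|---|---|---|
| Fatal-course deaths moved to days 2-3 | 2.5 to 5.7 | −0.34 to −0.80 | −0.61 to −1.37 | +1.01 to +2.31 |
| Same, plus 5 points of late deaths | 7.5 to 11 | −0.33 to −0.80 | −0.55 to −1.36 | +1.15 to +2.51 |
| 10 points of sudden deaths in improving patients | about 10 | +0.09 to +0.11 | +0.21 to +0.23 | +1.25 to +1.32 |
| 10 points of deaths after worsening | 8.1 to 8.6 | +0.39 to +0.42 | +0.69 to +0.73 | +0.70 to +0.75 |

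In the first two rows a significant false benefit occurred in 13% to 50% of runs on the day 1-9 mean. On the day-9 value it occurred in 23% to 74% (first row) and 21% to 75% (second row). In the third row, harm was significant in only 3% to 6% of runs. With no difference between arms, false benefit and false harm each occurred in about 2% to 4% of runs.

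**5. Credit for saved lives.** A separate simulation (assumed baseline 9, SD 3, placebo 9-day mortality about 14%; 60,000 per arm) halved the death hazard and left the SOFA course unchanged. The carried-forward means were 7.86 and 7.85, a difference of 0.01. With days after death scored 24 they were 8.91 and 8.38, a difference of 0.53.

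**The case against.** The strongest reply is that the article never says days after death are missing values. The full protocol or analysis plan, not shown, may score death separately, and a condensed article need not repeat that. This stands as a limit: freezing at death is the literal reading, not an express statement. It does not remove the point, because the article states a rule without exception and that rule suits this endpoint badly.

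Second, a reader might infer that a lethal drug will generally look beneficial. That is not supported. A check under assumed inputs, with hazard rising with SOFA and placebo day-9 mortality about 11%, doubled the hazard with no effect on SOFA. The carried-forward mean moved from 7.71 to 7.80, slightly towards harm. With a SOFA benefit growing to 1.4 points by day 9, the apparent benefit was 0.61 at hazard ratio 1 and 0.53 at hazard ratio 2, so extra deaths reduced it. Reversal needs deaths before SOFA has risen.

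Third, mortality is compared at days 28 and 90, and a safety board reviews the first 140 patients, so excess deaths would not go unreported. That is fair, but the article itself says mortality is not powered.

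Three further inferences fail:

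- *That patients lost before day 28 or 90 are carried forward as alive.* Time-to-event endpoints go to Cox regression, and Table 1 schedules survival as its own item to day 90.
- *That SOFA components are collected only when ordered*, from "haemoglobin and absolute platelet count (if available); biochemistry (if available); coagulation (if available); blood gasses (if available". The SOFA score is listed separately without that qualifier, and Table 1 schedules SOFA and laboratory tests on every day from 1 to 15.
- *That the standard errors are wrong.* Each patient contributes one summary value, and a check under no effect gave 4.8% type I error. The objection is to what is being estimated.

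**Conclusion.** The point holds in this form: the only stated rule, read literally, carries the last SOFA before death or before any other gap forward as if the patient were alive and unchanged. It gives little or no weight to deaths, can understate harm, and can reverse its sign when deaths come before SOFA has risen. The per-protocol analysis changes who is analysed, not how death is scored, so it is no safeguard.

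On the day 1-9 mean, the assumed courses give anything from harm shown at a little over half its death-as-worst size (about 0.4 against 0.7), through harm nearly invisible (about 0.1), to a false benefit of up to 0.80. Read at day 9, the false benefit reaches 1.37, close to the whole target effect. Baseline SOFA, day-9 mortality, the SOFA courses and the worst score of 24 are all assumptions; the article fixes none of them. The mechanism is secure, but its direction in this trial is not known.

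**What to change.** Replace the carrying-forward sentence with three statements:

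1. Missing SOFA values in living patients are handled by multiple imputation or a mixed model under missing at random.
2. Days after death, up to day 9 or day 15, are not filled by carrying forward and are not treated as ordinary missing data.
3. A death-as-worst analysis is prespecified and reported beside the primary result, at least as a sensitivity analysis. It is either rank-based with deaths placed last, or scores days after death as 24.

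If the full protocol or analysis plan already has a rule for death, the article's sentence should be aligned with it.

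The cost is a wording change before unblinding and slightly more analysis work. Making death-as-worst the primary analysis is a debatable choice, because it turns an organ-dysfunction endpoint into one weighted by death, and it costs precision. In simulation the SD rose from about 3.7 to 4.5-5.0, against the planned 3.2. At 117 per arm and an unchanged 1.4-point difference, power would be Φ(1.4 / (SD × √(2/117)) − 1.96), or 66% at SD 4.5 and 57% at SD 5.0. A treatment that also prevents deaths would recover some of this: with the hazard halved, simulated power was 63% with death scored 24 and 44% under carrying forward. With no effect on death and a larger SOFA effect, it was 42% against 65%. If that route is taken, the SD should be rechecked blind. As a sensitivity analysis, death-as-worst leaves the sample size untouched.
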